## Abstract

**Introduction:**

With no cure or effective treatment, the prevalence of patients with Alzheimer’s disease (AD) is expected to intensify, thereby increasing the social and financial burden on society. Light-based 40 Hz brain stimulation is considered a novel treatment strategy for patients with AD that may alleviate some of this burden. The clinical trial ALZLIGHT will utilize a novel Light Therapy System (LTS). The LTS uses Invisible Spectral Flicker for non-invasive induction of 40 Hz neural activity. This protocol describes a trial evaluating the efficacy and safety of a light-based 40 Hz brain stimulation in patients with mild-to-moderate AD.

**Methods:**

62 patients with mild-to-moderate AD will participate in a randomized, double-blinded, placebo-controlled, parallel-group, and single-center trial. The participants will partake in an enrollment period of 1 month, an intervention period of 6 months, and a 1.5-month post-interventional follow-up period. Prior to the baseline measurement (week 0), the patients will be randomized to either active or placebo intervention from baseline (week 0) to post-intervention follow-up (week 26).

**Discussion:**

This protocol describes a randomized, double-blinded, placebo-controlled clinical trial that may increase the understanding of the effect of gamma oscillations in the human brain and how it could be utilized as a novel and important tool for the treatment of AD. The effect is measured through a large, multidisciplinary assessment battery.

**Clinical trial registration:**www.ClinicalTrials.gov, (NCT05260177). Registered on March 2, 2022.

## Introduction

1.

Alzheimer’s disease is the most common type of dementia with an enormous disease burden that is expected to impact over 40 million patients globally (Nichols et al., 2019). Early this year, the FDA granted accelerated approval for Lecanemab (FDA U.S. Food and Drug Administration, 2023), an amyloid-modifying therapeutic agent that was found to reduce cognitive decline in early AD patients by 27% over the 18 months of treatment (Reardon, 2023; van Dyck et al., 2023). Even though this is an important progression in finding treatment options, the approval has not been without controversy, and the safety, costs, and clinical relevance to patients and caregivers are discussed (The Lancet, 2022; Reardon, 2023). Amyloid-modifying therapeutic agents were found to carry the risk of causing Amyloid-related imaging abnormalities (ARIA) with edema or effusions (Sperling et al., 2011; Cogswell et al., 2022), which are reported with Lecanemab (Reardon, 2023; van Dyck et al., 2023). Consequently, new and safe treatment options are still needed.

Alternatively, the induction of gamma activity has been proposed as a possible novel approach to treating AD by exposure to flickering lights (McDermott et al., 2018; Adaikkan and Tsai, 2020). This idea leans on mice studies indicating that exposure to 1 h daily 40 Hz stroboscopic light leads to a reduction of Aβ, tau protein (Iaccarino et al., 2016; Adaikkan et al., 2019), and even improved visuospatial memory when combined with 40 Hz auditory stimulation (Martorell et al., 2019). The proposed mechanism is not perfectly understood, but it indicates that gamma entrainment directly affects GABAergic interneurons and leads to activation and/or recruitment of microglia, resulting in the reduction of Aβ and tau protein (McDermott et al., 2018; Singer et al., 2018; Adaikkan and Tsai, 2020). Similar mechanisms are observed in studies using Transcranial Magnetic Stimulation (TMS) which also causes increased gamma activation (Barr et al., 2009). Thus, the induction of gamma activity is a promising new approach to the treatment of AD.

Entrainment of a specific frequency of neural oscillations by exposure to stroboscopic light at the same frequency is well established (Herrmann, 2001). It is even used in routine electroencephalography (EEG) with stable reactions with increasing age (Kasteleijn-Nolst Trenité et al., 2012; Zibrandtsen et al., 2020).

Studies in patients with AD using non-invasive light for 40 Hz entrainment remain limited. Previous light-based studies used stroboscopic light for entrainment and either no sham or a sham of non-flickering white light with no blinding of the study participants for obvious reasons (Ismail et al., 2018; Hajos et al., 2020; Chan et al., 2021; Cimenser et al., 2021). The importance of blinding procedures is well established. It is essential when subjective measures are used, such as in scoring symptoms by either the patient, the caregivers, or study personnel (Day, 2000).

This study will use a novel form of light called Invisible Spectral Flicker (ISF) (Carstensen et al., 2020). ISF alternates between two color profiles to achieve a 40 Hz flicker which is perceived as uniformly non-flickering by the observer, as ongoing studies in our group investigate. Therefore, the participants, the caregivers, the study personnel, and the data analysts can all be blinded throughout the study.

In conclusion, the objective of the trial is to investigate the effect of 40 Hz non-invasive ISF stimulation and assess the possibility of ISF as a novel treatment option for AD.

## Methods

2.

### Aim, study design, and setting

2.1.

This study will examine whether the entrainment of 40 Hz neural oscillation by novel 40 Hz Invisible Spectral Flicker is a potential therapy for AD. The study design will be a randomized, double-blinded (investigator, participant), placebo-controlled clinical trial. One arm of the study will receive active treatment with 40 Hz ISF, while the other arm will receive a placebo consisting of an identical sham device with non-flickering white light. The study will be conducted at the Zealand University Hospital, which is host to the regional memory clinic and the main diagnostic institution for neurological disease in the region of Zealand with an approximate population of 842.000 people (Danmarks Statistik, 2021). The intervention will last for 6 months (26 weeks) followed by 6 weeks of no intervention, see Figure 1. Those 6 weeks are designed to assess whether any potential effects are persisting after acute treatment.

**Figure 1 fig1:**
[figure not shown]
Flowchart of the study design.

### Participants

2.2.

This study will recruit a minimum of 62 patients with mild to moderate AD. Recruitment will continue until each arm reaches the target of 31 included participants. The participants must be above the age of 55, provide informed consent and match the following in- and exclusion criteria.

Inclusion criteria:

– Diagnosed with probable mild to moderate AD based on the National Institute on Aging and Alzheimer’s Association (NIA-AA) criteria (Jack et al., 2018)– Speak Danish fluently– >8 years of education– Pass a color-blindness test (Ishihara color test)– Have visual and auditory capabilities, and language skills necessary for neuropsychological testing– Participants must have a designated caregiver, who is available to support the participant in complying

Exclusion criteria:

– Visual acuity >0.5– Significant abnormalities related to relevant parts of the brain, e.g., the visual system, prefrontal cortex, or hippocampus, or relevant lesions detected by pre-trial imaging– Prior history of diseases related to the brain or the visual system (excluding AD)– Use of antiepileptic medication, neuromodulatory medication or high doses of sedatives– History of substance abuse within the last 2 years– Any significant systemic illness or unstable medical condition, which could lead to difficulty complying with the protocol (at the discretion of the PI)

### Intervention

2.3.

In both arms of this trial, participants will be instructed to sit in front of a specialized light source (henceforth “the device”) for 1 h daily during the intervention period of 6 months. The device must be within arm’s reach (at 50–100 cm distance), and the participants are instructed to face the device, see Figure 2A. The treatment group will have the device programmed to deliver 40 Hz ISF (Figure 2B), whilst the placebo group will have a sham device programmed to deliver non-flickering white light (Figure 2B) at the same intensity (~150 lux at the level of the eye) and color temperature (3,191 K, chromaticity coordinates of (x,y) = (0.410, 0.376)) as the treatment arm, equal to ISF and CONT in Agger et al. (2022). The devices used in this study will be the LTS 1.1 (Optoceutics ApS), the active setting in the device is equal to what is used in EVY LIGHT^®^ and NSS^®^ (Optoceutics ApS).

**Figure 2 fig2:**
[figure not shown]
Study Intervention. **(A)** Intervention setup during daily stimulation. The participants are instructed to sit in front of the device at an arm’s length distance (50-100 cm distance). **(B)** Mechanism of the active intervention using Invisible Spectral Flicker (ISF) alternating between Set 1 and Set 2 and of the placebo intervention.

### Blinding and randomization

2.4.

The light device can be set to either ISF or sham, meaning that there is no visual difference between the devices used for active treatment or the sham devices used for placebo. Thus, neither the participant, the caregivers nor the investigators will be able to differentiate the devices and can, therefore, remain blinded throughout the study.

Allocation of study participants will be done by a prefabricated random allocation list, created by a biostatistician which allocates consecutively enrolled participants to group A or group B. A or B corresponds to either treatment or sham, determined by the biostatistician through a flip of a coin. This assignment will be kept separate from the allocation list. When all data are recorded, the investigator will be informed of the allocation A or B, but not of which are sham or active treatment, which will only be revealed upon completion of group-level analysis. The principal investigator will have an allocation list available to be used in case of serious adverse events (SAE’s) to assess whether the SAE has consequences for the continuation of the study.

### Measurements

2.5.

At the inclusion visit (week −3 to 0), after giving informed consent, the following baseline characteristics will be recorded during a pre-screening: Age (years), gender (male/female), ethnicity (White, black, or others), height (cm), weight (kg), alcohol use in units (one unit defined as 12 g pure alcohol), tobacco use (package years), time since diagnosis of AD (months) and education (years). The participants will further have their medical history reviewed including current medication, physical examination, and blood samples (plasma-Alat, plasma-HbA1C, plasma-Sodium, plasma-Potassium, and plasma-Creatinine), this is done to rule out any undiagnosed diseases and establish baseline values in case of adverse events. To assess the effects of the treatment, the following examination battery will be administered at baseline (week 0), post-intervention follow-up (week 26), and no-intervention follow-up (week 32): EEG steady state visual evoked potential (SSVEP) during exposure to the allocated device (not at week 32), resting-state electroencephalography (rs-EEG) (Cassani et al., 2018), Alzheimer’s Disease Assessment Scale-Cognitive Subscale Plus Executive Function & Functional Ability (ADAS-Cog Plus EF&FA) (Skinner et al., 2012), Alzheimer’s Disease Cooperative Study – Activities of Daily Living (ADCS-ADL) (Galasko et al., 1997), Montreal Cognitive Assessment (MoCA) (Nasreddine et al., 2005), Magnetic resonance (MR) imaging (high-resolution T1-weighted imaging, functional Blood Oxygen Level Dependent imaging (BOLD-fMRI), perfusion-weighted MR imaging and MR spectroscopy) and blood-based biomarkers (plasma Aβ42/40-ratio, plasma tau181, plasma tau231, plasma neurofilament light chain, and plasma glial fibrillary acidic protein). In addition to these time-specific measurements, continuous actigraphy will be collected by a wrist-worn actigraph to assess activity and changes in the circadian rhythm. All data will be recorded by trained personnel. The EEG will be recorded in a designated room, shielded from outside electrical interference using 25 gel-mounted electrodes arranged according to the international 10–20 system with additional electrooculographic (EOG) and electrocardiographic (ECG) electrodes. The cognitive testing will be performed by trained personnel with experience in neuropsychological testing. The MR scan will be performed on a 3T scanner (Siemens Magnetom Vida, Siemens Healthcare). Actigraphy will be recorded using a wrist-worn actigraph (ScanWatch, Withings).

### Outcome measures

2.6.

Primary outcome:

The goal is to determine the total gamma power, with no concomitant LTS device stimulation, and to assess changes in the gamma power at around 40 Hz measured with power spectral density and EEG SSVEP from baseline (week 0) to post-intervention follow-up (week 26).

Null hypothesis: There is no significant difference between treatment and placebo in total gamma power and power spectral density signal-to-noise ratio at baseline (week 0) and follow-up (week 26).Research hypothesis: There is a significant difference between treatment and placebo in total gamma power and power spectral density signal-to-noise ratio at baseline (week 0) and follow-up (week 26).

The statistical analysis plan will be available before the data collection of the study is completed.

Secondary outcomes:

The secondary outcomes include exploratory outcomes which are listed below. All refer to the change from baseline (week 0) to post-intervention follow-up (week 26), and no-intervention follow-up (week 32), unless otherwise specified.

Change in ADAS-Cog Plus EF&FAChange in ADCS-ADLChange in MoCAChange in resting-state BOLD-fMRI connectivity in the default mode network (DMN)Change in rs-EEG connectivity encompass alpha-theta with DMNChange in MR spectroscopy NAA/mI-ratioChange in total sleep time and wakefulness after sleep onsetChange in blood-based biomarkers of AD (plasma Aβ42/40-ratio, plasma tau181, plasma tau231, plasma neurofilament light chain, and plasma glial fibrillary acidic protein)Change in global atrophy (ventricular volume) and in hippocampal volumeChange in MR Arterial Spin labeling (ASL) perfusion in the posterior cingulate gyrus, precuneus, inferior parietal lobe, and lateral prefrontal cortexChange in rs-EEG spectral composition in the dominant alpha rhythm

In addition to these secondary endpoints, safety will be monitored by the number of Adverse Events (AE), and similarly, occurrences of ARIAs will be monitored. The compliance/adherence will be measured directly by the device which includes a camera with facial recognition software. This determines the number of days missed, the time present in front of the device as well as gaze direction to assess the time of direct exposure. Furthermore, compliance and feasibility will be evaluated via a structured interview that includes questions on the perception of flickering, brightness, and usability of the device.

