### Recruitment and sample size

2.8.

Participants will be recruited through contact with their usual healthcare professionals on the Danish Island of Zealand with a population of approximately 2.7 million inhabitants (Danmarks Statistik, 2021).

The sample size calculation is based on the primary outcome and has been based on effect sizes reported (Xing et al., 2018; Jones et al., 2019). The estimation is carried out using R version 3.6.3 with “pwr” version 1.2–2 with the following assumptions: (1) Two-sample *T*-test assuming equal variance, (2) Equal allocation, (3) Signal-to-noise (SNR) ratio at 40 Hz of 2.7 dB in the active treatment group and 0 dB in the placebo group at 6 months, (4) Standard deviation of 3.2 dB in both groups, (5) A power of 90%, and (6) Type 1 error of 5%. A 50% drop-out rate is assumed based on previous experience, resulting in a sample size of 124 (62 in each arm).

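### The primary outcome joins device-off gamma power with an SSVEP recorded on each arm's own device; as the hypotheses are written, the immediate response to the flicker can make the SNR component significant, and the stated 90% power covers only a 6-month level.

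*Protocol article*

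**What the plan says.** Section 2.6 names two quantities in one goal sentence. The first is device-off: "The goal is to determine the total gamma power, with no concomitant LTS device stimulation". The second is a change in power near 40 Hz, "measured with power spectral density and EEG SSVEP from baseline (week 0) to post-intervention follow-up (week 26". The null and research hypotheses then speak of a treatment-placebo difference in "total gamma power and power spectral density signal-to-noise ratio at baseline (week 0) and follow-up (week 26"), which is a comparison of levels at two visits. No rule says whether one or both quantities must succeed.

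Section 2.5 lists the recording as "EEG steady state visual evoked potential (SSVEP) during exposure to the allocated device (not at week 32"), separately from resting-state EEG. Section 2.3 describes the two stimuli: "The treatment group will have the device programmed to deliver 40 Hz ISF", while placebo participants have "a sham device programmed to deliver non-flickering white light". The abstract places randomisation before the week-0 measurement.

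The planning assumption in section 2.8 is "Signal-to-noise (SNR) ratio at 40 Hz of 2.7 dB in the active treatment group and 0 dB in the placebo group at 6 months", with SD 3.2 dB, a two-sample t-test, 90% power and 5% type 1 error. The Discussion says earlier work has already shown that ISF induces 40 Hz oscillations.

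**The concern.** The trial asks whether six months of daily 40 Hz light is a potential therapy. An SSVEP taken while each arm faces its own lamp compares a 40 Hz stimulus with no 40 Hz stimulus. Since the article itself expects ISF to evoke a 40 Hz response, an arm difference on that measure should appear at the first recording, before any home treatment. A significant week-26 difference in it would therefore not separate an acute response from a treatment effect.

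The goal, the hypotheses and the power calculation also describe different things: a change, a level at each of two visits, and a level at 6 months. The 90% power cannot apply to all of them. It has no stated link to the device-off measure, which is the one that bears most directly on the brain's own gamma activity.

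**Working it through.** **Inputs from section 2.8:** difference 2.7 dB, SD 3.2 dB per arm, alpha 0.05 (taken as two-sided; the article does not say), power 0.90. Section 2.2 gives 31 per arm as the target and section 2.8 gives 62 per arm after 50% drop-out. That discrepancy is a separate matter; both sizes are shown where useful.

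**Assumptions not in the article:** that the immediate on-device response is 2.7 dB in the active arm and 0 dB in placebo, and the correlation ρ between the week-0 and week-26 values.

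**1. The plan's own figure.** d = 2.7/3.2 = 0.844. The two-sample t-test needs 30.5, so 31 per arm. Dividing by 1 − 0.5 gives 62 per arm and 124 in total. The stated size reproduces, for a single comparison of levels.

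**2. Levels compared at week 26, with an immediate response and no six-month effect.** The standard error is 3.2 × √(2/31) = 0.813 dB and the noncentrality is 2.7/0.813 = 3.32. The probability of significance is 0.905 with 31 per arm and 0.997 with 62. The same calculation holds at week 0, because that SSVEP is also taken on the allocated device. Simulation gave about 0.90 at both visits with 31 per arm.

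**3. Change from week 0.** Let b be the active arm's on-device response at week 0, with 2.7 dB at week 26 and 0 dB in placebo at both visits. The expected difference in change is 2.7 − b, and the SD of change is 3.2 × √(2(1 − ρ)), which is 3.2 dB at ρ = 0.5. With 31 per arm and ρ = 0.5:

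| b (dB) | Difference in change (dB) | Probability of significance |
|---|---|---|
| 0 | 2.70 | 0.90 |
| 1.35 | 1.35 | 0.37 |
| 2.7 | 0 | 0.05 |

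For b = 1.35 the figure runs from 0.28 (ρ = 0.3) to 0.95 (ρ = 0.9); with 62 per arm and ρ = 0.5 it is 0.64. For b = 2.7 it is 0.05 at any size, which is the correct error rate, since no six-month effect exists in that case.

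**4. Week 26 adjusted for the on-device week-0 value.** Adjustment removes only ρ × 2.7 dB, which leaves an expected difference of 2.7 × (1 − ρ), or 1.35 dB at ρ = 0.5. Simulated rejection with 31 per arm and no six-month effect was 58%, 40%, 25% and 11% for ρ = 0.3, 0.5, 0.7 and 0.9. Covariate adjustment therefore does not protect the on-device measure as a simple change does.

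**5. Device-off gamma power.** The article gives neither an effect size nor an SD identified as belonging to this measure, so no power can be calculated.

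**The case against.** Four points on the other side have force.

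- **The device-off measure comes first.** It addresses the trial's question and is not open to the lamp artefact. A reader might infer that a positive primary result would show only that the cortex follows the flicker; the documents do not support that, because device-off gamma power is part of the outcome.
- **Some readings block the false positive.** The goal sentence speaks of change, and on a strict change analysis a stable immediate response cancels. The hypotheses join the two quantities with an *and*; if both must succeed, the lamp response alone is not enough. These readings are available, but the text does not choose them.
- **The origin of the 2.7 dB is not stated.** A reader might take 2.7 against 0 dB to be the device-on contrast, since 0 dB in placebo fits it. Section 2.8 does not say whether the device was on or off, so this remains inference. Treating the hypotheses' SNR as the SSVEP measure is likewise the natural reading rather than an explicit statement.
- **The week-0 response is unknown.** A reader might infer that power for change falls to 5% on the protocol's own numbers. That needs the full 2.7 dB at week 0, unchanged at week 26, and the article gives no week-0 figure.

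The article defers to an analysis plan that is not shown, and that plan may name the contrast and the success rule. It could choose among the quantities, but it could not make one power calculation apply to all of them.

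**Conclusion.** The point holds as a defect of definition; the sample-size arithmetic is sound. The primary outcome mixes a device-off and a device-on measure with no rule for which decides, and its goal, hypotheses and power refer to different quantities. Under the hypotheses as written, the SNR component can be significant in about 90% of trials with 31 per arm and no six-month effect, provided that the immediate response is 2.7 dB with SD 3.2 dB. It becomes a false efficacy claim only if levels are compared and the SNR component alone suffices, which the article neither states nor rules out.

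If change is analysed, power at 31 per arm and ρ = 0.5 lies anywhere from 0.90 down to 0.05, depending on an unstated week-0 response. The 90% in section 2.8 is established only for a level at 6 months. This should be settled before unblinding, because it governs what a positive result would mean.

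**What to change.** **Section 2.6.** Rewrite the hypothesis as a between-arm difference in change from week 0 to week 26, or in the week-26 value adjusted for baseline. Make device-off gamma power, from the resting-state EEG already recorded, the measure that decides the efficacy conclusion, and state that the device is off. Keep the allocated-device SSVEP as a target-engagement measure that cannot support efficacy alone. Baseline adjustment should be used only with the device-off measure, for the reason in step 4.

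**Section 2.8.** State whether the 2.7 against 0 dB was measured with the device on or off, and restrict the 90% power to that quantity. For the device-off measure, give the assumption and the power, or say that none is available.

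**Cost.** Changes to the wording of the protocol and analysis plan and a registry update, with no new procedure. The real price is that the stated power for the deciding measure becomes less favourable or unknown. An alternative is to test change in SSVEP with both arms under the same stimulus, but section 2.5 does not describe such a recording, so it would mean changing the procedure.
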